## Abstract

**Background:**

Although percutaneous coronary intervention (PCI) is becoming the standard therapy in ST-segment elevation myocardial infarction (STEMI), to date most patients, even in developed countries, are reperfused with intravenous thrombolysis or do not receive a reperfusion therapy at all. In the post-lysis period these patients are at high risk for recurrent ischemic events. Early identification of these patients is mandatory as this subgroup could possibly benefit from an angioplasty of the infarct-related artery.

Since viability seems to be related to ischemic adverse events, we initiated a clinical trial to investigate the benefits of PCI with stenting of the infarct-related artery in patients with viability detected early after acute myocardial infarction.

**Methods:**

The VIAMI-study is designed as a prospective, multicenter, randomized, controlled clinical trial. Patients who are hospitalized with an acute myocardial infarction and who did not have primary or rescue PCI, undergo viability testing by low-dose dobutamine echocardiography (LDDE) within 3 days of admission. Consequently, patients with demonstrated viability are randomized to an invasive or conservative strategy. In the invasive strategy patients undergo coronary angiography with the intention to perform PCI with stenting of the infarct-related coronary artery and concomitant use of abciximab. In the conservative group an ischemia-guided approach is adopted (standard optimal care).

The primary end point is the composite of death from any cause, reinfarction and unstable angina during a follow-up period of three years.

**Conclusion:**

The primary objective of the VIAMI-trial is to demonstrate that angioplasty of the infarct-related coronary artery with stenting and concomitant use of abciximab results in a clinically important risk reduction of future cardiac events in patients with viability in the infarct-area, detected early after myocardial infarction.

## Background

Management of acute myocardial infarction (AMI) has underwent considerable changes in the last two decades and the management of patients with AMI has become more established [1,2]. In patients with ST-segment elevation myocardial infarction (STEMI), primary angioplasty is becoming first-choice therapy [2-4]. However, because of the low availability of such treatment, even in developed countries, most patients with STEMI are reperfused with intravenous thrombolysis. Many patients do not receive a reperfusion therapy at all [5,6].

Data from large clinical trials indicate that after successful thrombolysis more than 50% of patients have a significant residual stenosis and about 30% of patients have spontaneous or inducible ischemia [7-9]. In this group reocclusion of the infarct-related artery is a potential threat, as it is associated with recurrent ischemia or recurrent infarction [10,11]. Therefore, early risk assessment is of great importance, especially in patients treated with thrombolysis and patients who did not receive reperfusion therapy. This risk assessment should be followed by an effective treatment strategy in order to prevent recurrent cardiac events and deterioration of left ventricular function [12,13]. As these recurrent events are mainly due to the presence of an unstable residual stenosis of the infarct-related coronary artery, an effective therapy should include an invasive procedure like angioplasty to optimize coronary flow to the infarct area in high risk patients [11].

Trials have been performed to study the effect of routine angioplasty on clinical outcome early after AMI treated with thrombolysis [14-20]. Most of these studies failed to show improvement of clinical outcome with a standard invasive approach. Possible explanations for these results are the unselected approach, and the high risk profile of balloon angioplasty in the early days, when abciximab and stents were not available. Because angioplasty always carries an inherent risk, it remains important to select those patients after a recent myocardial infarction, who will actually benefit from angioplasty of the infarct-related artery.

To date, non-invasive risk stratification after AMI has mainly focused on exercise stress testing. The inability to exercise, the low diagnostic accuracy and resting ECG abnormalities, however, remain important limitations in the detection of ischemia [21].

Several post-infarction observational studies investigated viability as prognosticator and showed that the presence of viability in the infarct area was highly predictive for future coronary events like recurrent ischemia, recurrent infarction, left ventricular failure, and death [22-31]. Viable tissue is potentially jeopardized by an unstable residual stenosis in the infarct-related coronary artery. In a meta-analysis of non-randomized data by Iskandrian, the impact of revascularization on clinical outcome in patients with viability after AMI was studied [32]. A significant decrease in future cardiac events was observed in the patients with viability who were revascularized. In contrast, the outcome in patients without viability in the infarct area did not change by an invasive strategy.

In this context it should be noted that other post-infarction studies have shown viability to be associated with an improved prognosis [33-36]. Two studies demonstrated that especially patients with severe LV dysfunction and viability show a better survival than patients with LV dysfunction but without viability [34,36]. The reason for this paradox is not quite understood. However, it can be argued that patients with viability have a potential of recovery of LV function (spontaneous or by revascularization), thereby improving their survival [37]. Thus, on one hand viability may improve survival by recovery of function especially in patients with moderate to severe LV dysfunction, on the other hand viability is related to a worse prognosis by increased risk of recurrent ischemic events.

Based on the aforementioned assumptions, we initiated a clinical trial to investigate the benefits of percutaneous coronary intervention (PCI) of the infarct-related artery in patients with viability detected in the early, subacute phase of myocardial infarction. To demonstrate viability, we use low-dose dobutamine echocardiography (LDDE). This test can safely be performed 48 hours after acute MI [23,27,30,31]. It is a well validated bedside test with a diagnostic accuracy of about 80%, which is comparable to scintigraphical techniques (SPECT/PET) [38]. Coronary stenting will be performed with concomitant use of abciximab. After stenting, oral clopidogrel is given in a standard way. With this approach the lowest possible periprocedural event rate will be attained, with a low rate of target vessel revascularization (TVR) [39-43].

We hypothesize that, in order to prevent future cardiac events, PCI is only useful in patients with viability in the infarct zone early after myocardial infarction.

## Methods

### Patient Selection

Patients admitted to any of the participating centers with an acute or recent myocardial infarction, who are not treated by direct or rescue angioplasty, and who are stable during the first 48 hours after the acute event, are screened for the study. Patients < 80 years of age are considered suitable for the study when they have definite myocardial infarction, as demonstrated by an significant rise in creatine kinase-MB levels (twice the upper limit of normal: ULN), 1 mm ST segment elevation in two or more standard leads or 2 mm ST segment elevation in two contiguous chest leads, and/or the development of Q waves.

The criteria for exclusion are: viability testing technically not possible (poor echo-window), contraindications for dobutamine echocardiography (arrhythmia), and coronary angiography (severe diabetic nephropathy or known contrast-allergy), serious life-threatening non-cardiac illness, ECG abnormalities making the evaluation of the ST segment impossible (left bundle branch block, pacemaker), and an unreliable follow-up.

The study complies with the Declaration of Helsinki and all ethics committees of the participating centers have approved the protocol. All eligible patients provide written informed consent.

### Study design

The study is a prospective, multicenter, randomized, controlled clinical trial. In the VIAMI-trial, patients who are admitted to the hospital with an acute myocardial infarction and who did not undergo primary or rescue PCI, are evaluated by LDDE within 3 days of admission. Patients with unequivocal signs of viability in the infarct-area are randomized to an invasive or a conservative treatment strategy. In the invasive strategy patients undergo coronary angiography with the intention to perform PCI with stenting of the infarct-related coronary artery. In the conservative group an ischemia-guided approach is adopted with stress testing before discharge from the hospital. When the test is highly suggestive for ischemia, coronary angiography will be performed. If revascularization is performed, this will be scored as a secondary endpoint. Patients without viability will serve as a registry group with long-term follow-up (Fig 1). These patients are assigned to the conservative group in order to prevent physicians' bias during the trial.

**Figure 1 F1:**
[figure not shown]
Flow chart

The primary endpoint is the composite of death from any cause, recurrent infarction, and unstable angina. The secondary endpoints are need for revascularization, the occurrence of angina pectoris (CCS classification), and the incidence of heart failure (NYHA classification). Left ventricular function is also evaluated as determined by echocardiography at 3 months, 6 months, and 1 year follow-up.

A reinfarction is diagnosed if there is an increase in the total creatine kinase and MB isoenzyme activity (2 times ULN) and either a history of ischemic chest discomfort, or electrocardiographic changes indicative for transmural ischemia or necrosis.

For the diagnosis of unstable angina, the patient must be hospitalized with ischemic chest pain or discomfort occurring at rest or with minimal exertion. In addition, the need for intravenous medical intervention and/or objective evidence of myocardial ischemia is required. For extensive description of the end points definitions, see Table I.

**Table I T1:** Primary end point definitions

**Definition of reinfarction**
1. Reinfarction during hospitalization for index infarct and not related to revascularization procedures - Either ischemic type of chest discomfort or new electrocardiographic changes indicative for transmural ischemia or necrosis with an increase in the total creatine kinase and MB isoenzyme activity. The activity of CK-MB has to be at least 2 times the upper limit of normal and more than 50% above the previous baseline value.
2. Reinfarction discharge for index infarct and not related to revascularization procedures - Either a history of ischemic chest discomfort, usually lasting > 20 minutes, or classic electrocardiographic changes indicative for transmural ischemia with an increase in the total creatine kinase and MB isoenzyme activity of at least 2 times the upper limit of normal. - New abnormal Q-waves (amplitude ≥ 1/3 of total QRS amplitude and ≥ 0.04 seconds) in ≥ 2 contiguous leads.
3. Periprocedural reinfarction during revascularization after index infarct PCI - Classic electrocardiographic changes indicative for transmural ischemia with an increase in the total creatine kinase and MB isoenzyme activity of at least 2 times the upper limit of normal. - New abnormal Q-waves (amplitude ≥ 1/3 of total QRS amplitude and ≥ 0.04 seconds) in ≥ 2 contiguous leads.
CABG
- Classic electrocardiographic changes indicative for transmural ischemia with an increase in the total creatine kinase and MB isoenzyme activity of at least 5 times the upper limit of normal. - New abnormal Q-waves (amplitude ≥ 1/3 of total QRS amplitude and ≥ 0.04 seconds) in ≥ 2 contiguous leads.
**Definition of unstable angina**
- Ischemic type of chest discomfort at rest or with minimal exertion, with a duration of at least 15 minutes. The presenting symptoms must represent a change from the patients' usual anginal pattern. - Either a need for intravenous medical intervention and/or objective evidence of myocardial ischemia (dynamic ST changes in ≥ 2 contiguous electrocardiographic leads, or an abnormal elevation of Troponin-T or Troponin-I without a significant rise of CK MB isoenzyme activity)

PCI, percutaneous coronary intervention; CABG, coronary artery bypass grafting; CK-MB, creatine kinase myocardial enzyme

A clinical endpoints and safety monitoring committee will continuously check and monitor all events in a blinded manner. Reinfarction after revascularization will be scored as described in Table I. Major and minor bleeding complication in the invasive treated group are defined according to the criteria of the Thrombolysis in Myocardial Infarction trials [44]. All patients will be treated with aspirine, beta blockers, angiotensin-converting-enzyme inhibitors and statins as accepted in international guidelines [2,4].

### Low-dose dobutamine echocardiography

If the inclusion criteria are met and none of the criteria for exclusion, viability testing by LDDE is performed within 3 days of admission.

Preferably, beta-blockers are withdrawn 24 hours before the test [23,27,30,31]. Discontinuation of beta-blockers seems to to enhance LDDE accuracy [45,46]. Before the administration of dobutamine, a baseline echocardiogram is obtained according to the guidelines of the American Society of Echocardiography [47]. Five standard views are obtained: the parasternal long-axis and short-axis view and the apical two, three- and four-chamber view. A 16-segment model is used in which the apex is divided in 4 segments. Segmental wall motion and thickening is scored according to a 4-point scale: 1 = normal, 2 = hypokinetic, 3 = akinetic, and 4 = dyskinetic. Left ventricular volumes and ejection fraction are measured by use of the modified Simpson's rule algorithm from orthogonal apical long-axis projections as recommended by the American Society of Echocardiography.

Dobutamine is administrated intravenously at doses of 5, 10, and 15 μg/kg/min, for 5 minutes at each dose. When a 10% increase in heart rate is not achieved with 15 μg/kg/min, a 5-minute infusion with 20 μg/kg/min can be used as the final stage of the procedure.

Viability is defined as the improvement of wall motion abnormalities in two or more segments of the infarct zone. Changes from hypokinesia to normokinesia and from dyskinesia or akinesia to hypo- or normokinesia are considered an improvement in wall motion abnormality. Dyskinesia changing to akinesia is not considered as an improvement. Patients are continuously monitored by a 12 lead ECG and blood pressure is recorded at the end of each stage. All views are recorded at rest and during dobutamine on VHS videotape. All videotapes are sent to the core-lab (VU University medical center) and will be analyzed by 2 experienced observers. A third observer is used in case of disagreement to reach consensus.

For subsequent off-line analysis, the echocardiographic images will be digitized from VHS videotape and transferred to a working station (Enconcert^® ^by Philips). The images will be displayed side-by-side in a quadscreen format to facilitate the comparison of images.

### Coronary angiography and angioplasty

Angiography and angioplasty will be performed as soon as possible after randomization. Coronary angiography will be performed according to standard protocols. To determine the severity of culprit lesions, quantitative coronary arteriography (QCA) will be performed to measure percent diameter stenosis, reference diameter and cross-sectional area stenosis. The degree of stenosis will be determined in the view in which the stenosis is most severe.

When feasible, PCI will be performed (with or without etc) when there is a significant (≥ 50%) stenosis or occlusion of the infarct-related coronary artery, with the intention to perform primary stenting of the infarct-related artery, with concomitant use of abciximab, according to the EPILOG protocol [39] After stenting, all patients recieve oral clopidogrel in a standard way. In case of severe 3-vessel disease or significant left main stem stenosis, where PCI is judged to be a high risk, coronary artery bypass grafting will be considered.

### Follow-up

Patients will be followed for a period of three years. Follow-up data will be obtained of all patients during visits at the outpatient clinic in the first year, and by telephone interview in the second and third year of follow-up. Left ventricular function (volumes and ejection fraction) is determined by echocardiography at 3 months, 6 months, and 1 year of follow-up.

### Statistical design

The VIAMI-trial is conducted to investigate the differences in clinical outcome between an invasive and a conservative strategy in patients with demonstrated viability in the infarct-area. The expected event rate in the viability positive group is estimated to be 35 percent. To demonstrate with a power of 80% (α = 0.05, two-sided) that PCI leads to a 50% reduction in event rate in the invasive group compared to the conservative group, 200 patients will be needed in each group. Therefore, we intend to randomize a total of 400 patients in this trial, with interim analysis after 200 included patients.

The formal stopping rules for the study are the following: If one of the treatment strategies appears significant superior at interim analysis (P ≤ 0.01), the study will be stopped.

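### The stated inputs (35% event rate, 50% reduction, 80% power, two-sided 0.05) need about 99 patients per group, not the 200 given, and no stated allowance explains the difference

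*Protocol article*

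**What the plan says.** All the figures are in the Statistical design section of the protocol article.

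- Event rate: "The expected event rate in the viability positive group is estimated to be 35 percent".
- Effect: "PCI leads to a 50% reduction in event rate in the invasive group compared to the conservative group".
- Error rates: power 80%, "α = 0.05, two-sided".
- Result: "200 patients will be needed in each group", and so "we intend to randomize a total of 400 patients in this trial".
- Interim look: "with interim analysis after 200 included patients", with early stopping at P ≤ 0.01.

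The section names no formula and no inflation for dropout, crossover or the interim look. The Statistical analysis section lists chi-square or Fisher's exact tests for proportions, a log-rank test for event-free survival, and intention-to-treat analysis.

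**The concern.** The paragraph prints every input and the result, so it can be checked directly, and a standard calculation gives about half the printed number. The size of a randomised trial is normally justified by this one statement. If it does not add up, a reader cannot tell which treatment effect the 400 patients were chosen to detect, or whether the design allows for something that is not disclosed. The placing of the interim look is also affected. It is presented as a look at half the planned enrolment, but the same paragraph's inputs imply a whole trial of about that size.

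**Working it through.** **Inputs.** From Statistical design: p1 = 0.35 (read as the conservative arm), p2 = 0.5 × 0.35 = 0.175, two-sided alpha 0.05 (z = 1.960), power 80% (z = 0.8416), equal groups. The difference is 0.175 and the mean rate is 0.2625.

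**Step 1: try to reproduce 200 per group.** The pooled two-proportion formula is

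n = [1.960 × √(2 × p̄ × (1 − p̄)) + 0.8416 × √(p1(1 − p1) + p2(1 − p2))]² / (p1 − p2)²

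- First term: 1.960 × √(2 × 0.2625 × 0.7375) = 1.960 × 0.6222 = 1.2196
- Second term: 0.8416 × √(0.2275 + 0.1444) = 0.8416 × 0.6098 = 0.5132
- n = (1.7328)² / 0.030625 = 98.05, so 99 per group and 198 in total

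The printed figure is not reproduced: 200 / 99 = 2.02.

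**Step 2: vary the method and the reading.**

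| Variant | Per group |
|---|---|
| Unpooled variance | 96 |
| Continuity correction | 110 |
| Fisher's exact test | about 109–110 |
| Log-rank, hazard ratio ln(0.825)/ln(0.65) = 0.447 | 94 (Schoenfeld), 103 (Freedman) |
| Log-rank, hazard ratio 0.50 | 122–126 (Schoenfeld), 131–136 (Freedman) |
| Final alpha lowered to 0.04 for the interim look | 105 (116 corrected) |
| Alpha 0.01 | 147 (158 corrected) |
| 90% power instead of 80% | 131 (142 corrected) |
| 35% read as the average over both arms | 65 |

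With 35% taken as the control rate, the two-sided variants at alpha 0.05 and 80% power run from 94 to 136 per group. The excess is therefore about 1.5-fold (200/136) to 2.1-fold (200/94).

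**Step 3: what 200 per group delivers.**

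- Power for 35% versus 17.5%: (0.175 × √200 − 1.2196) / 0.6098 = 2.058, which is 98.0%. With a final alpha of 0.04 it is 97.5%.
- Solving for p2 at 80% power gives 0.224. The relative reduction is 1 − 0.224/0.35 = 36%.

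**Step 4: the interim look.** With 100 per group, (0.175 × √100 − 1.2196) / 0.6098 = 0.870, which is 81% power at alpha 0.05 if follow-up is complete. In number of patients, the interim is the whole trial that the stated inputs call for. This does not hold for information: the Current status section says the interim patients had 30-day follow-up, and the stopping level was 0.01.

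**Step 5: the allowance needed to reach 200.** These are assumptions, since the article states none.

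- Dropout of 50%: 99 / (1 − 0.50) = 198.
- Crossover of 30% from conservative to invasive: the control rate becomes 0.35 − 0.30 × 0.175 = 0.2975. Against 0.175 this needs 188 per group.
- Crossover of 20%, with 90% of the invasive arm receiving PCI: 0.315 versus 0.1925 needs 197 per group.

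**The case against.** The strongest defence is dilution. Under Study design, conservative patients whose stress test strongly suggests ischemia go to angiography and may be revascularised. The Background puts spontaneous or inducible ischemia after successful thrombolysis at about 30%. Under Coronary angiography and angioplasty, PCI in the invasive arm depends on feasibility and on a stenosis of at least 50%. The analysis is by intention to treat. A planner who believed that PCI halves the risk in those who receive it, and who allowed for such mixing, could arrive near 200 with every printed rate intact. An article also condenses the full protocol, where the derivation may be given.

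Part of this stands. Dilution is plausible, so an input need not be wrong. It does not rescue the sentence, which words the 50% as the reduction between the randomised groups and calls 200 per group the number needed for it. If dilution was the basis, the assumed difference between groups is not 35% versus 17.5%, and the paragraph should say so.

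A reader might infer that the power, the effect or the event rate must be misstated. The documents do not support that. The sample size itself may be the slip: 2 × 99 = 198 is close to 200, as if a total had been entered as a per-group figure. A reader might also note that 20% versus 10% needs 199 per group and conclude that the true control rate was 20%. Nothing in the article points to 20%. Other pairs, such as 35% versus 22.4%, fit 200 equally well, so the match identifies nothing.

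**Conclusion.** The sample-size statement is wrong as written: the printed number is about twice what the printed inputs need by the usual formula. This rests on taking 35% as the conservative-arm rate, equal groups and no dilution or loss. Reading 35% as the average over both arms widens the gap. Which element is at fault cannot be settled from the article.

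The severity is moderate. A reader might infer that the trial lacks its stated 80% power, but on the stated assumptions it has more than that. Nor does the slip make a null result uninterpretable, because the confidence interval at analysis shows which effects are excluded. No estimate is biased. What is affected is the stated reason for randomising 400 patients and the description of the interim as a look partway to the required size.

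**What to change.** Keep the planned enrolment, retrieve the original calculation, and name the method used. Then make whichever correction it supports:

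1. If no allowance was intended and the inputs are right, state that 200 per group gives about 98% power for 35% versus 17.5%, and 80% power for 35% versus about 22%, in each case before any dilution by crossover.
2. If crossover or dropout was allowed for, state the allowance and the difference between groups that is assumed after it.
3. If an input or the per-group number was misstated, correct it. If it was the number, say that about 99 per group meets 80% power and give the reason for enrolling 400.

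The cost is one corrected paragraph, with no change to enrolment or conduct.

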### Current status

Enrollment of patients started April 1, 2001. Recently, an interim analysis was performed after the inclusion of 200 patients, having a 30 day follow-up. The Clinical Event Committee recommended continuation of the trial.

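### The article sets an efficacy stop at P ≤ 0.01 but states no reduced final level; a final test at 0.05 would put the overall type I error at 5.5% to just under 6%

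*Protocol article*

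**What the plan says.** Three statements in Methods, Statistical design, matter here.

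- **Design level.** The size calculation is introduced by "To demonstrate with a power of 80% (α = 0.05, two-sided"; this is the only alpha given for the trial. The inputs are an expected event rate of 35% and a halving of it, and the result is that "200 patients will be needed in each group".
- **Interim.** The plan is to "randomize a total of 400 patients in this trial, with interim analysis after 200 included patients".
- **Stopping rule.** Under a sentence that calls the rules formal: "If one of the treatment strategies appears significant superior at interim analysis", with P ≤ 0.01 as the criterion, the study is stopped. The rule works in both directions and names no length of follow-up.

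Neither this section nor Statistical analysis gives a level for the final test, a spending function, or a statement that the 0.01 comes out of the 0.05.

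Current status then reports that "an interim analysis was performed after the inclusion of 200 patients, having a 30 day follow-up", and that the trial continued. The Abstract defines the primary endpoint over three years.

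**The concern.** A rule that permits a claim of superiority at the interim is a test and uses part of the type I error. If 0.01 is available at the interim and the full 0.05 at the end, the two together exceed 0.05. The less information the interim shares with the final analysis, the weaker the correlation between the two tests, and the closer the total comes to the simple sum of 0.06.

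A boundary of P ≤ 0.01 is not strict enough to ignore. A final P a little below 0.05 could be reported as significant at the 5% level when, counting both looks, it is not. Continuing after the interim does not remove the problem, because the rule allowed rejection at that look.

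**Working it through.** **Inputs from the article.** Two-sided alpha 0.05; power 80%; event rate 35%, read as the conservative-arm rate; 50% reduction, so 17.5%; 200 per group; one interim after 200 of 400 patients; interim boundary P ≤ 0.01, taken as two-sided because either strategy may win.

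**Assumed input.** The information fraction t at the interim is not stated. It is varied from 0 to 0.5, because 200 of 400 patients with incomplete follow-up should carry at most about half of the final information.

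**Step 1. The plan's own figure.** For two proportions,

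n = [z(0.975)·√(2p̄(1−p̄)) + z(0.80)·√(p₁(1−p₁) + p₂(1−p₂))]² / (p₁−p₂)²

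with p₁ = 0.35, p₂ = 0.175 and p̄ = 0.2625:

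n = [1.960 × 0.6222 + 0.8416 × 0.6098]² / 0.175² = 3.003 / 0.030625 = 98.05, so 99 per group (110 with continuity correction).

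The stated 200 per group is not reproduced. That is a separate matter. It is relevant here only because 200 per group leaves ample power to pay for a lower final level.

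**Step 2. Overall type I error if the final test is at 0.05.** Let Z₁ and Z₂ be the interim and final statistics, bivariate normal under the null with correlation √t. Then

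overall error = P(|Z₁| ≥ 2.576 or |Z₂| ≥ 1.960) = 0.01 + 0.05 − P(both).

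At t = 0 the two are independent, so P(both) = 0.01 × 0.05 = 0.0005 and the total is 0.0595. The other values come from the bivariate normal distribution. A simulation gave 0.0547 at t = 0.5 and 0.0585 at t = 0.1.

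**Step 3. Final level that restores 0.05.** Solve P(|Z₁| ≥ 2.576 or |Z₂| ≥ c) = 0.05 for c and convert c to a two-sided P.

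| Information fraction t | Overall error, final test at 0.05 | Final level that gives 0.05 overall |
|---|---|---|
| 0.5 | 0.0546 | 0.0452 |
| 0.25 | 0.0572 | 0.0425 |
| 0.2 | 0.0577 | 0.0421 |
| 0.1 | 0.0586 | 0.0412 |
| 0.05 | 0.0591 | 0.0408 |
| towards 0 | 0.0595 | 0.0404 |

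A plain split, 0.01 + 0.04 = 0.05, bounds the error whatever t is.

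**Step 4. Power at 200 per group, 35% versus 17.5%.**

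power = Φ{[0.175·√200 − z·0.6222] / 0.6098}

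- Final level 0.05 (z = 1.960): Φ(2.058) = 98.0%.
- Final level 0.04 (z = 2.054): Φ(1.963) = 97.5%.

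At a final level of 0.04, 80% power needs 105 per group (116 with continuity correction), well within 200.

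**The case against.** The strongest reply is that the article never says the final test is run at 0.05. The 0.05 stands in the sample-size sentence as the design level. An interim at P ≤ 0.01 is compatible with an overall 0.05 if the final level is about 0.040 to 0.045, and a full protocol or analysis plan could say so. This stands in part. A reader might infer that the trial's type I error is in fact above 5%; the document does not support that, and the excess is conditional on the final level. What remains is more than detail left to another document. The article itself fixes a formal rejection rule and a single alpha, and applied together as stated they do not deliver that alpha.

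A second tempting reading is that the stopping rule was written for 30-day data, so that a stop would by design have answered only a 30-day question. The rule names no follow-up. The 30 days appear only in the report of the interim that was done, and that wording could mean at least 30 days for each patient, with more for those enrolled early. Statistical analysis also lists primary endpoint analyses at 30 days, 6 months and 1 year, so the final horizon is itself not uniform in the article. A low information fraction is therefore plausible but not established.

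Third, the calculation assumes that the interim test attains its nominal 1%. Statistical analysis allows Fisher's exact test where appropriate. With 100 per group and assumed null event rates of 5.25% to 14% (15% to 40% of the 35%), its true size at a nominal 0.01 is about 0.004 to 0.006. The overall error would then be at most about 5.4% to 5.6%. This shrinks the excess if Fisher's test was used, but does not remove it.

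**Conclusion.** The point holds conditionally. The article sets an efficacy stop at P ≤ 0.01 and one trial alpha of 0.05, and reserves none of that alpha for the interim. If the final test uses 0.05, the overall two-sided error is 5.46% at an information fraction of 0.5 and up to 5.95% as the fraction approaches zero, an excess of about 0.5 to 1.0 percentage points. This rests on the normal approximation, on an interim test that attains its nominal level, and on an assumed range for the information fraction. The error exceeds 5% throughout that range.

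Severity is modest. The conclusion changes only if the final P falls between the adjusted level (about 0.04 to 0.045) and 0.05. Under the design effect, the chance of a final P between 0.04 and 0.05 is about 98.0 − 97.5 = 0.5 percentage points.

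**What to change.** Before the final analysis, add one sentence to Statistical design: because P ≤ 0.01 was available at the interim, the final primary test uses two-sided 0.04, so that the overall alpha is at most 0.05. This is valid at any information fraction and needs no further calculation.

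Alternatively, state that the final level will be calculated from the actual share of primary events available at the interim. This gives about 0.041 at a share of 0.1 and 0.045 at a share of 0.5. If the full protocol or analysis plan already sets such a level, cite it here.

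The cost is small. At 0.04, power for 35% versus 17.5% with 200 per group falls from 98.0% to 97.5%. For a smaller effect, a reduction of about 36%, it falls from 80% to 77%. The planned total of 400 does not change.
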